## Abstract

**Background:**

Alcohol use is directly related to over 3 million deaths worldwide every year. Contingency management is a cost-effective treatment for substance use disorders; however, few studies have examined its efficacy for alcohol use disorder. Recent technological advances have enabled the combined use of mobile apps and low-cost electronic breathalyzer devices to remotely monitor alcohol use. Leveraging this type of technology, our study group has recently developed an integrated contingency management system that would enable community treatment programs to remotely deliver contingency management to anyone who owns a smartphone.

**Objective:**

In this paper, we present a full description of our integrated contingency management system, Automated Reinforcement Management System (ARMS), and describe a protocol that will evaluate its feasibility and usability.

**Methods:**

Initially, 6 clinicians will participate in a 1-hour focus group where the study staff will navigate through ARMS as it would be used by clinicians and patients. Clinicians will provide feedback on the intervention in general, which will be used to modify ARMS to make it more user friendly, time saving, and relevant to treatment. A second focus group will summarize the changes made following the initial clinician feedback and will provide additional input regarding the potential utilization of ARMS. Thereafter, the clinicians’ acceptability of ARMS will be evaluated using the System Usability Scale. Following the clinicians’ assessments of ARMS and final modifications, the system will be evaluated in terms of feasibility and patient usability by using an A-B-A within-subject experimental design wherein 20 treatment-seeking individuals with alcohol use disorder will be recruited. The two A phases (control conditions) will each last 2 weeks, and the B phase (contingency management condition) will last 4 weeks. During all phases, participants will be asked to use the ARMS app to submit three breathalyzer samples per day (at 10 AM, 2 PM, and 8 PM). Participants will be prompted by the ARMS app at these predetermined times to record and submit their breathalyzer samples. During the A phases, participants will earn vouchers for every breathalyzer sample submitted, independent of their sample results. During the B phase, vouchers will be provided contingent upon the submission of alcohol-negative breathalyzer samples (breath alcohol content = 0.00). At the end of the A-B-A experiment trial, patients’ usability of the ARMS app will be evaluated using the System Usability Scale. Feasibility will be measured based on whether the ARMS app helped significantly increase alcohol abstinence.

**Results:**

Recruitment for this study began in January 2021 and is expected to be completed by December 2021.

**Conclusions:**

This study will provide the baseline capability for the implementation of a remotely monitored contingency management platform. If successful, ARMS has the potential to provide effective treatment for alcohol use disorders to individuals living in remote rural areas.

## Introduction

Alcohol use is directly related to over 3 million deaths worldwide each year (ie, 5.3% of all deaths reported annually) and is a casual factor of more than 200 diseases, injuries, and conditions [1]. In the United States, the lifetime and past-year prevalence of alcohol use disorder (AUD) are 29.1% and 13.9%, respectively [2], making it the most prevalent substance use disorder in the country [3].

Contingency management is an effective treatment for substance use disorders that consists of providing reinforcement (ie, rewards) after an objective verification of drug abstinence through the submission of a substance-negative biospecimen [4-6]. Although the efficacy of contingency management has been demonstrated for a range of substance use disorders [7-9], fewer studies have examined the efficacy of contingency management for AUD [10-14]. This was primarily due to the lack of biomarkers that could detect alcohol consumption for prolonged periods. Until recent years, the only commercially available biomarker for alcohol use was breath alcohol content (BAC), assessed using breathalyzers that measure the concentration of ethanol in an individual’s breath [15,16]. Although accurate, this biomarker can only detect alcohol use for up to 12 hours after consumption; moreover, when used infrequently, it is a tool better used to assess intoxication rather than abstinence [14]. As a result, to accurately assess recent alcohol consumption, contingency management interventions using a breathalyzer require individuals to be physically present at an office or treatment center to submit samples multiple times per day [14], limiting the feasibility of such an approach.

Fortunately, recent technological advances have enabled the combined use of mobile apps and low-cost consumer electronic breathalyzer devices to remotely monitor alcohol use [17,18]. Studies wherein smartphone apps and remote breathalyzers were used to provide contingency management for AUD have found them to be effective in promoting alcohol abstinence [17,19,20]. Although other technologies, such as prescription digital therapeutics (eg, reSET and reSET-O by Pear Therapeutics), have been approved by the US Food and Drug Administration (FDA) for substance use disorders, they have not directly targeted substance abstinence. As a result, to date, app-based contingency management technologies for alcohol use have yet to be integrated into AUD treatment programs and evaluated in community treatment settings.

To further advance research on the use of technology to address AUD and to enable the development of more effective treatment strategies, our research group has partnered with Managed Health Connections [21] to develop an integrated, end-to-end contingency management system that would enable community treatment programs to deliver contingency management remotely to anyone who owns a smartphone and seeks to reduce their alcohol consumption. In this methods paper, we present a full description of an integrated contingency management system, termed Automated Reinforcement Management System (ARMS), and describe the protocol that will evaluate its feasibility and usability.

## Methods

### Participants

This study will be conducted within the community and with community clinic partners in Spokane, WA, USA, under the auspices of the Washington State University Program of Excellence in Addictions Research at the Analytics and PsychoPharmacology Laboratory. In this phase 1 study, a total of 6 clinicians and 20 patients will be recruited. Patients of either biological sex who are 18 years of age or older and have an Alcohol Use Disorders Identification Test (AUDIT) [22] score of 8 or higher will be eligible to enroll in the study. Participants must read and speak English and have the ability to provide written informed consent. Patients with severe AUD or a co-occurring psychotic disorder according to the Diagnostic and Statistical Manual of Mental Disorders, Fifth Edition (DSM-V) [23], with significant risk of dangerous alcohol withdrawal (defined as a history of alcohol detoxification or seizure in the last 12 months and expression of concern by the individual about dangerous withdrawal), or with a lifetime suicide attempt or suicidality in the past year will not be eligible for enrollment in the study.

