Once the modifications are made in response to the second wave of clinician feedback, ARMS will be evaluated primarily for efficacy but also for feasibility and patient usability through an A-B-A (or, “return-to-baseline”) completely within-subject experimental design. Following similar single subject-design studies conducted by our group [20,24], the two A phases will each last 2 weeks and the B phase will last 4 weeks, for a total study duration of 8 weeks. During all phases, participants will be asked to use the ARMS app to submit breathalyzer samples at 10 AM, 2 PM, and 8 PM each day. Submission of each sample should take less than 5 minutes. Participants will be prompted by their ARMS app to record and submit their breathalyzer samples at these predetermined times and will have a half-hour window following the prompt to submit each sample. During the A phases (control conditions), participants will earn US $2 in vouchers for every breathalyzer sample submitted during the predetermined period, independent of their sample results. Notably, this reward system will be in effect for both the first and second A phases. During the B phase (contingency management condition), vouchers will be provided contingent upon the submission of alcohol-negative breathalyzer samples—that is, breath alcohol content (BAC) = 0.00. Participants will begin by receiving vouchers worth US $2 per alcohol-negative breath sample submitted, with the value escalating by US $0.25 per alcohol-negative sample submission to a maximum value of US $3.50 per submission. Vouchers will be reset to US $2 per sample if a participant does not submit a sample in the predetermined period, if an alcohol-positive breath sample is submitted, or if the participant cannot be identified from the facial recognition photo (see details below).

At the end of the A-B-A experiment trial, the patients’ acceptability of ARMS will be evaluated with the System Usability Scale (SUS).

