### Assessments

Assessments collected in this study will include sociodemographic and medical or treatment history data, the Mini-International Neuropsychiatric Interview [25], Addiction Severity Index-Lite (ASI) [26], Brief Symptom Inventory (BSI) [27], DSM-V [23], Fagerström Test for Nicotine Dependence [28], AUDIT [22], Alcohol Urge Questionnaire (AUQ) [29], and 15D Health-Related Quality of Life (HRQoL) [30]. Alcohol use will be measured using the Alcohol Timeline Follow Back (ATFB) method [31], and BAC results will be collected via the ARMS app. Both the providers’ and patients’ acceptability toward ARMS will be evaluated using the SUS [32]. For the assessment schedule, see Table 1.

**Table 1 table1:** Assessment schedule for the A-B-A design experimental trial.

Content	Baseline	A-B-A							
	Week 0	Week 1	Week 2	Week 3	Week 4	Week 5	Week 6	Week 7	Week 8
Informed consent	✓								
Sociodemographic	✓								
Medical/treatment history	✓								
DSM-V^a^	✓								
Mini-International Neuropsychiatric Interview	✓								
Addiction Severity Index: ASI-Lite	✓		✓		✓		✓		✓
15D Health-Related Quality of Life	✓		✓		✓		✓		✓
Alcohol Urge Questionnaire	✓	✓	✓	✓	✓	✓	✓	✓	✓
Fagerström Test for Nicotine Dependence	✓		✓		✓		✓		✓
Alcohol Use Disorders Identification Test (AUDIT)	✓	✓	✓	✓	✓	✓	✓	✓	✓
Brief Symptom Inventory (BSI)	✓		✓		✓		✓		✓
Alcohol use (biochemical BAC^b^)	✓	3 times per day							
Alcohol Timeline Follow Back (self-report)	✓	✓	✓	✓	✓	✓	✓	✓	✓
Patient acceptability: System Usability Scale		✓	✓	✓	✓	✓	✓	✓	✓

^a^DSM-V: Diagnostic and Statistical Manual of Mental Disorders, Fifth Edition.

^b^BAC: blood alcohol content.

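### As worded, a recent seizure excludes a patient with non-severe AUD and no detoxification history only if the patient also voices concern about withdrawal

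*Protocol article*

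**What the plan says.** The Participants section of the protocol article lists the eligibility rules. Patients must be adults with an AUDIT score of at least 8, read and speak English, and be able to consent. One sentence then gives the exclusions:

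- "Patients with severe AUD or a co-occurring psychotic disorder";
- a significant risk of dangerous withdrawal, "defined as a history of alcohol detoxification or seizure in the last 12 months and expression of concern by the individual about dangerous withdrawal";
- any lifetime suicide attempt, or suicidality in the past year.

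The Abstract states that "20 treatment-seeking individuals with alcohol use disorder will be recruited". Under Study Design, phase A lasts two weeks and pays for any submitted sample. In phase B, which lasts four weeks, "vouchers will be provided contingent upon the submission of alcohol-negative breathalyzer samples", meaning BAC = 0.00. The voucher rises from US $2 to US $3.50 in steps of US $0.25 and resets to US $2 after a positive or missed sample. The Assessments section says "Assessments collected in this study will include sociodemographic and medical or treatment history data", and Table 1 places these at week 0.

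**The concern.** The withdrawal exclusion is a safety rule. Its parenthesis says what the risk is 'defined as' rather than giving examples, so it sets the rule. Within it, a seizure in the past year counts only when the patient also says that he or she is worried. A patient who does not recognise the risk, or who plays it down, passes the criterion despite an objective warning sign.

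From week 3 the same patient would be paid only for alcohol-free samples, submitted remotely. Reduced drinking is what the intervention aims for, so this is the setting in which the withdrawal exclusion has to work.

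**Working it through.** No sample size or error rate enters this point, and the article gives no figure to reproduce. The check is of the logic.

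**Inputs, from the Participants section.** Let D = detoxification history, S = seizure in the last 12 months, C = concern voiced by the patient. Each is 0 or 1, which gives 2 × 2 × 2 = 8 profiles.

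**Readings.** The plain wording allows two groupings:

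- R1: (D or S) and C
- R2: D or (S and C)

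A third reading takes 'and' as listing alternative grounds, R3: D or S or C. It is shown for comparison, although it is not what the sentence says.

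| D | S | C | R1 | R2 | R3 |
|---|---|---|---|---|---|
| 0 | 0 | 0 | admitted | admitted | admitted |
| 0 | 0 | 1 | admitted | admitted | excluded |
| 0 | 1 | 0 | **admitted** | **admitted** | excluded |
| 0 | 1 | 1 | excluded | excluded | excluded |
| 1 | 0 | 0 | admitted | excluded | excluded |
| 1 | 0 | 1 | excluded | excluded | excluded |
| 1 | 1 | 0 | admitted | excluded | excluded |
| 1 | 1 | 1 | excluded | excluded | excluded |

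Only one seizure profile is admitted under both R1 and R2: seizure, no detoxification, no voiced concern. The two profiles with detoxification but no concern depend on the grouping, so nothing is claimed about them except that the sentence leaves them unclear.

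**Other criteria.** Severe AUD, psychotic disorder and suicidality are separate grounds, and none of them is triggered by a seizure. The inclusion rules do not mention seizure. The profile therefore stays eligible if AUD is non-severe and the other grounds are absent.

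**Check of the proposed wording.** Split S into Sa (alcohol-related or undetermined cause) and So (any other cause). The proposed rule is F: Sa or ((D or So) and C).

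- Against R1, which becomes (D or Sa or So) and C: if C = 1 with Sa = 1, F excludes through its first part. If C = 1 with D = 1 or So = 1, F excludes through its second part. Every patient excluded under R1 stays excluded, and F adds those with Sa = 1 and C = 0.
- Against R2: a patient with D = 1, Sa = 0 and C = 0 is excluded under R2 but not under F. If the sponsor meant R2, detoxification must be written as a ground of its own, F2: D or Sa or (So and C).

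The split matters. A replacement that mentioned only alcohol-related seizures and dropped the old clause could admit a patient with a seizure of another cause and voiced concern. If 'seizure' in the current text means any seizure, that patient is excluded today.

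**The case against.** The strongest reply is that the article packs every exclusion into one sentence. The authors may have meant the history and the concern as alternative grounds (R3), under which the gap disappears. The document does not say, so that intention cannot be ruled out. It is not the plain wording, though, and if it was intended the sentence still needs correcting.

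A second reply is that the full protocol may hold itemised criteria or a medical clearance rule. That is fair, and it limits the point to the definition as stated. A reader might infer that such patients are in fact being enrolled; the article does not show that.

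Third, other features offer some protection. The Provider Interface section describes alerts and a list that puts patients who are nonadherent or missing their goals at the top. Baseline also includes a psychiatric interview and the ASI-Lite. These bear on how serious the gap is, but none is an eligibility rule.

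Fourth, the conjunction may be deliberate, to protect recruitment. That could justify making detoxification conditional on concern, and the choice can stay with the sponsor. It is a weaker reason for making a seizure conditional.

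**Conclusion.** The point holds for the text as written. Under either plain grouping, a patient with non-severe AUD, a seizure in the last 12 months, no detoxification history and no voiced concern is not excluded. It is a narrow gap in a safety criterion and worth correcting.

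Three stronger conclusions are tempting but not supported:

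- A reader might infer that anyone with a recent seizure and no voiced concern can enter. Severe AUD is excluded in the same sentence, and under R2 a detoxification history excludes alone.
- A reader might want a probability that one of the 20 patients fits the profile. The document gives no prevalence, so any such figure would rest on an invented share. The number is probably small.
- A reader might infer that phase B forces complete abstinence. It pays for alcohol-free samples at three set times a day; a positive or missed sample costs the voucher and resets its value.

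The conclusion assumes that 'and' carries its ordinary meaning. It does not depend on whether 'alcohol' also modifies 'seizure', since a withdrawal seizure is covered either way.

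**What to change.** Reword the definition so that significant withdrawal risk means either of the following:

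- (a) any seizure in the last 12 months that is alcohol-related or of undetermined cause, regardless of voiced concern; or
- (b) a history of alcohol detoxification or any other seizure in the last 12 months, together with expressed concern about dangerous withdrawal.

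If detoxification was meant to exclude alone, say so and move it to a ground of its own.

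Recruitment began in January 2021, so also check enrolled patients' baseline medical and treatment history. Anyone who fits the profile should not start phase B without medical review.

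**Cost.** A short amendment, a review of records already collected at week 0, and a medical review for anyone identified. No new assessment is needed: the present criterion already requires seizure and detoxification history, and a seizure of unclear cause falls under (a) by default. The downside is a rare extra screen failure and a slightly narrower population.

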### Study Design

To evaluate the feasibility and usability of ARMS delivered in treatment settings, our research team has designed a three-step study where ARMS will be evaluated by both treatment providers and patients. Initially, 6 clinicians will participate in a 1-hour-long interview or focus group (depending on their availability) that will describe and provide visuals of the contingency management intervention and introduce patient- and provider-facing apps. Study staff will navigate through the program in ways consistent with both clinician and patient users. Clinicians will also participate in a semistructured interview where they will be asked to provide information on their standard protocol when working with patients who have AUD, such as how they currently track progress and communicate with patients. Furthermore, they will be asked to provide feedback on the intervention in general, including why they would or would not use the app, suggestions for improvement, app usability, potential obstacles that may be encountered with the use of the app, preferences for accessing the data generated by the app, and preferences on which data they would prefer to have highlighted briefly.

The information provided by the clinicians in this first focus group will then be used to modify ARMS to make it more user friendly, time saving, and relevant to treatment (possibly by incorporating new features that may assist treatment). A second focus group will then summarize the changes made following the clinician feedback and provide deidentified user data allowing clinicians to navigate through the system and provide additional feedback regarding the potential utilization of patient data.

Once the modifications are made in response to the second wave of clinician feedback, ARMS will be evaluated primarily for efficacy but also for feasibility and patient usability through an A-B-A (or, “return-to-baseline”) completely within-subject experimental design. Following similar single subject-design studies conducted by our group [20,24], the two A phases will each last 2 weeks and the B phase will last 4 weeks, for a total study duration of 8 weeks. During all phases, participants will be asked to use the ARMS app to submit breathalyzer samples at 10 AM, 2 PM, and 8 PM each day. Submission of each sample should take less than 5 minutes. Participants will be prompted by their ARMS app to record and submit their breathalyzer samples at these predetermined times and will have a half-hour window following the prompt to submit each sample. During the A phases (control conditions), participants will earn US $2 in vouchers for every breathalyzer sample submitted during the predetermined period, independent of their sample results. Notably, this reward system will be in effect for both the first and second A phases. During the B phase (contingency management condition), vouchers will be provided contingent upon the submission of alcohol-negative breathalyzer samples—that is, breath alcohol content (BAC) = 0.00. Participants will begin by receiving vouchers worth US $2 per alcohol-negative breath sample submitted, with the value escalating by US $0.25 per alcohol-negative sample submission to a maximum value of US $3.50 per submission. Vouchers will be reset to US $2 per sample if a participant does not submit a sample in the predetermined period, if an alcohol-positive breath sample is submitted, or if the participant cannot be identified from the facial recognition photo (see details below).

At the end of the A-B-A experiment trial, the patients’ acceptability of ARMS will be evaluated with the System Usability Scale (SUS).

### Assessments

Assessments collected in this study will include sociodemographic and medical or treatment history data, the Mini-International Neuropsychiatric Interview [25], Addiction Severity Index-Lite (ASI) [26], Brief Symptom Inventory (BSI) [27], DSM-V [23], Fagerström Test for Nicotine Dependence [28], AUDIT [22], Alcohol Urge Questionnaire (AUQ) [29], and 15D Health-Related Quality of Life (HRQoL) [30]. Alcohol use will be measured using the Alcohol Timeline Follow Back (ATFB) method [31], and BAC results will be collected via the ARMS app. Both the providers’ and patients’ acceptability toward ARMS will be evaluated using the SUS [32]. For the assessment schedule, see Table 1.

**Table 1 table1:** Assessment schedule for the A-B-A design experimental trial.

Content	Baseline	A-B-A							
	Week 0	Week 1	Week 2	Week 3	Week 4	Week 5	Week 6	Week 7	Week 8
Informed consent	✓								
Sociodemographic	✓								
Medical/treatment history	✓								
DSM-V^a^	✓								
Mini-International Neuropsychiatric Interview	✓								
Addiction Severity Index: ASI-Lite	✓		✓		✓		✓		✓
15D Health-Related Quality of Life	✓		✓		✓		✓		✓
Alcohol Urge Questionnaire	✓	✓	✓	✓	✓	✓	✓	✓	✓
Fagerström Test for Nicotine Dependence	✓		✓		✓		✓		✓
Alcohol Use Disorders Identification Test (AUDIT)	✓	✓	✓	✓	✓	✓	✓	✓	✓
Brief Symptom Inventory (BSI)	✓		✓		✓		✓		✓
Alcohol use (biochemical BAC^b^)	✓	3 times per day							
Alcohol Timeline Follow Back (self-report)	✓	✓	✓	✓	✓	✓	✓	✓	✓
Patient acceptability: System Usability Scale		✓	✓	✓	✓	✓	✓	✓	✓

^a^DSM-V: Diagnostic and Statistical Manual of Mental Disorders, Fifth Edition.

^b^BAC: blood alcohol content.

